#### Data management

During the study, the investigator regularly enters information into case report forms (CRFs). Database management and quality control of this study are the responsibility of a biostatistician. Structured data elements from the CRFs are entered into the database and reviews using double data entry for verification. Electronic data are kept in a duplex database—one available in the hospital department and the other available at one of the Safety Committee member’s department. Information entered into the database is systematically checked and obvious errors are corrected. Omissions or questions are returned to the investigator for resolutions. Paper data related to our study are preserved in the 2nd Department of Coronary Artery Disease.

### Statistical analysis

Comparison of categorical variables (sinus rhythm restoration, AF recurrence, serious adverse reactions, safety outcome) between groups will be performed using the χ^2^ test of independence with Yate’s correction, or with Fisher’s exact test in cases of minimum expected count less than 5, and these will be expressed as number and percentage.

After initial assessment of the quantitative variables’ distributions (time to sinus rhythm restoration, SBP, DBP, HR), measures of location and dispersion will be calculated—as arithmetic mean and standard deviation for normally distributed variables, or as median and quartile range for variables for which the Shapiro–Wilk test null hypothesis has been rejected. For comparison of continuous variables between the two groups, the unpaired Student’s *t* test (or Cochran’s *C* test in the case of heteroscedasticity of variance) will be used, or for skewed data, the nonparametric Mann–Whitney *U* test. Differences for matched samples (within groups) will be evaluated with McNemar’s test, paired Student’s *t* test or Wilcoxon’s rank sum test.

All probability values will be calculated from two-sided tests, and *P* < 0.05 will be considered statistically significant. All statistical analysis will be performed using SAS 9.42 software (SAS Institute Inc.). After inclusion of 20 patients, effectivity and safety analyses will be performed by the statistician, Safety Committee and principal investigator, who will have access to interim results and will make the final decision to continue or terminate the trial. Hypotheses will be tested according to the significance level set to α ≤ 0.05 with 2-sided tests. Statistical analysis will be conducted using SAS 9.2 software.

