**Methods:**

Eighty eligible patients with an episode of AF lasting less than 48 h are randomized in a 1:1 ratio to receive canrenone or placebo. Patients randomized to a treatment intervention are receiving canrenone intravenously at a dose of 200 mg within 2–3 min. Subjects assigned to a control group obtain the same volume of 0.9% saline within the same time. The primary endpoint includes return of sinus rhythm documented in the electrocardiogram within 2 h after drug or placebo administration. Other endpoints and safety outcomes analyses, due to expected lack of statistical power, are exploratory.

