When the 2-h observation period is over or when sinus rhythm returns, the ECG and blood pressure measurement valuation are performed. Further treatment of the patient will depend on their clinical condition and will follow appropriate clinical guidelines (Fig. 2) [1]. Enhanced monitoring for worsening of a subject’s condition and the use of standard rescue medications will be introduced in the case of need.

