### Statistical methods

#### Sample size estimation

The sample size analysis is based on the *Z* test for fractions in two independent samples.

One of the purposes of this analysis is to compare fractions from two populations, with the hypothesis of their equality being tested. The *Z* test will be performed for two independent tests, with a type I error rate (α) of 0.01. The test is two-sided, so both positive and negative deviation from the hypothesis value can be considered significant. We assume that the population fractions in the groups are 0.50 and 0.05. In order to achieve 90.00% power, assuming that the sample numbers in the two groups are equal, a sample size of at least *N* = 27 from each group is required. For *N* = 27, the power in each group is 90.40%.

Assuming an optimistic scenario (no dropout interest and a sample of 80 people): Φ = Cramer’s *V* = 0.50396; relative benefit 10.0 [2.50–39.98].

The purpose of the effect size is to avoid a statistically significant result resulting only from a huge sample size, not from clinical effectiveness. Such a situation would not occur in the presented research. In conclusion, to show superiority of canrenone over placebo, a sample size of 80 patients was calculated based on the following assumptions: a two-tailed test, a type I error of 0.01, a power of 90%, efficacy of placebo of 5% (evaluated according to three trials testing vernakalant), efficacy of canrenone of 50% and a 20% dropout rate to fulfill the criteria of intention-to-treat analysis [12–14]. Due to a presumed low frequency of events, the secondary and safety endpoints will be evaluated in an exploratory manner.

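### The between-arm test of AF recurrence has no interpretable denominator, and the outcome ECG and BP reading is tied to conversion

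*Protocol article*

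**What the plan says.** - **Recurrence.** The Endpoints section names return of AF during the observation period as a secondary endpoint. The Statistical analysis section puts it in one list with the primary outcome and the safety outcomes: "Comparison of categorical variables (sinus rhythm restoration, AF recurrence, serious adverse reactions, safety outcome) between groups will be performed using the" chi-square test with Yates' correction, or Fisher's exact test when the minimum expected count is below 5, reported as number and percentage. It does not say whether the percentage is of all randomised patients or of converters.
- **Timing.** The Study procedures section states: "When the 2-h observation period is over or when sinus rhythm returns, the ECG and blood pressure measurement valuation are performed". The same section says that each patient is observed for 2 h after the last bolus, and it lists continuous ECG monitoring and periodic non-invasive BP among the standard components of care. The Statistical analysis section then compares SBP, DBP and HR between and within groups, without saying which readings are used.
- **Planning rates.** Sample size estimation: "We assume that the population fractions in the groups are 0.50 and 0.05".
- **Status.** The secondary and safety endpoints are called exploratory.

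**The concern.** Every patient enters in AF, so recurrence requires prior conversion, which is the outcome the drug is meant to change. A plain comparison of recurrence between arms therefore mixes two things: how many patients became able to recur, and how often they did. Converters also have different amounts of the 2 h left in which to relapse, depending on when they converted.

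The timing rule raises a related problem. If the reading at conversion is the one analysed, a converter contributes an earlier value, taken in sinus rhythm, and a non-converter contributes a 2-h value taken in AF. The Discussion section of the abstract says that canrenone lowers BP, and the main Discussion says that its effect starts in 2 h. An arm with more early readings may thus differ in BP for reasons of timing and rhythm as well as drug effect.

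At stake are a secondary endpoint whose sign can be misread as a disadvantage of the drug, and BP and HR comparisons that are hard to interpret. An exploratory label does not correct a misleading sign, and the Statistical analysis section applies the 0.05 threshold to all tests.

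**Working it through.** **1. The plan's own figure.** Inputs: p1 = 0.50, p2 = 0.05, mean 0.275, difference 0.45, two-sided α = 0.01 (z = 2.576), power 90% (z = 1.282).

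n = [2.576·√(2·0.275·0.725) + 1.282·√(0.25 + 0.0475)]² / 0.45² = (1.627 + 0.699)² / 0.2025 ≈ 26.7, so 27 per arm.

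Power at 27 is 0.9040, which agrees with the article ("For *N* = 27, the power in each group is 90.40"%). The effect-size line for 80 patients corresponds to 20/40 versus 2/40: φ = (20·38 − 20·2)/√(40·40·22·58) = 0.504, and relative benefit 10.0 [2.50 to 39.99], matching the article apart from rounding. So 20 and 2 converters are the article's own scenario.

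**2. Patients able to recur.** 40 × 0.50 = 20 on canrenone; 40 × 0.05 = 2 on placebo.

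**3. All-randomised denominator.** P(recurrence) = P(conversion) × r, where r is the risk among converters. The documents give no r, so a range is assumed, equal in both arms. The table of recurrences in 40 versus 40 was enumerated exactly and tested by the article's rule at two-sided 0.05, the level in the Statistical analysis section ("Hypotheses will be tested according to the significance level set to α ≤ 0.05 with 2-sided tests").

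| r, both arms | Canrenone | Placebo | P(more recurrences on canrenone) | P(significantly more) |
|---|---|---|---|---|
| 10% | 5% | 0.5% | 0.82 | 0.01 |
| 20% | 10% | 1% | 0.95 | 0.15 |
| 30% | 15% | 1.5% | 0.99 | 0.40 |
| 40% | 20% | 2% | 0.996 | 0.62 |
| 50% | 25% | 2.5% | 0.999 | 0.79 |

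The ratio is always 0.50/0.05 = 10, whatever r is.

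Sensitivity:
- If canrenone halved the risk among converters (10% versus 20%, up to 25% versus 50%), it would still show more recurrences with probability 0.76 to 0.94, and significantly more with probability 0.01 to 0.19.
- Equal expected percentages need a risk among canrenone converters of 0.05/0.50 = one tenth of that on placebo.
- If canrenone converts only 30%, the probability of more recurrences is 0.63 to 0.97 and of significantly more 0.001 to 0.31, for equal r of 10% to 50%.

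**4. Converters-only denominator.** The percentages are then equal by construction when r is equal, but the placebo group has about 2 patients. The chance of no placebo converter is 0.95⁴⁰ = 12.9%. With 0 of 2, the exact 95% interval runs from 0 to 1 − 0.025^(1/2) = 84%. The groups compared are also no longer the randomised ones.

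**5. Composite in all randomised patients.** P(converted and still in sinus rhythm at 2 h) = P(conversion) × (1 − r). At r = 20% this is 0.50 × 0.80 = 40% versus 0.05 × 0.80 = 4%. The reversal disappears and randomisation is kept.

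**6. Timing.** If the reading at conversion is the one analysed, up to 20 of 40 (50%) on canrenone and 2 of 40 (5%) on placebo would be read before 2 h under the planning rates.

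**The case against.** The strongest reply is that the text does not say what a critic may read into it. It compares groups, and it does not say that all randomised patients form the denominator. A condensed article may leave the analysis set of an exploratory endpoint to the full protocol or SAP. That is correct, and a missing denominator alone would not be a finding. The point stands because neither obvious denominator gives an interpretable between-arm test, so stating one of them later would not repair it.

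Second, a reader might infer that canrenone will be shown to be worse. The documents do not support that. The recurrence risk is an assumption, and at 10% to 30% a nominally significant excess has probability 0.01 to 0.40. Only the expected direction follows from the planning rates, and only with the all-randomised denominator. The conversion result would also be reported beside it.

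Third, a reader might infer that BP is confounded, or that early converters have no 2-h ECG. Neither is established. The text does not say which BP and HR readings are compared, periodic BP and continuous ECG monitoring may supply 2-h values, and the schedule figure is not available here. What stands is conditional: if the assessment described in Study procedures feeds the comparison, its time depends on the outcome.

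Finally, these endpoints are exploratory, and the primary endpoint, sample size and power are untouched. That limits the weight of the point but does not remove it.

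**Conclusion.** The concern holds in a limited form. A between-arm test of AF recurrence is not interpretable as described. Over all randomised patients, equal risk among converters gives an expected 5% to 25% versus 0.5% to 2.5%, a tenfold excess created by conversion alone. Among converters, about 2 placebo patients remain and randomisation is lost. This rests on conversion rates of 50% and 5%, 40 analysed per arm, and an assumed recurrence risk of 10% to 50%. The direction is likely under those assumptions; nominal significance is better than even only towards the upper part of the range (0.62 at 40%).

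The ECG and BP assessment is stated at an outcome-dependent time. Whether this affects the SBP, DBP and HR comparisons depends on which readings are analysed, which the article does not say. Study procedures also leaves open whether observation runs to 2 h after an early conversion, although the recurrence window depends on it. The two statements there must be reconciled.

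**What to change.** 1. Replace the between-arm recurrence test, within the exploratory analyses, by the proportion converted and still in sinus rhythm at 2 h, in all randomised patients by assigned arm. Say how a patient who relapses and reconverts before 2 h is counted.
2. List recurrences among converters descriptively, with counts and times, and without a between-arm test.
3. Compare SBP, DBP and HR at a fixed 2 h in every patient, using the monitoring already in place. Keep the reading at conversion as an additional record.
4. Reconcile, in Study procedures, the 2-h observation of each patient with the assessment at return of sinus rhythm, so that the recurrence window is defined.

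Cost: one 2-h ECG, BP and HR recording in early converters, and revised wording. Recruitment has started, and the Study design section requires changes to outcomes and analyses to be reported to the regulator, the registry and the ethics committee, so an amendment notice is also needed. The primary endpoint and the sample size do not change.

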**Fig. 1 Fig1:**
[figure not shown]
Schedule of enrolment, interventions and assessments. AF atrial fibrillation, ECG electrocardiogram

Patients admitted to the Emergency department at the National Institute of Cardiology and diagnosis of a new onset atrial fibrillation are considered for participating in the study. Strategies for achieving adequate participant enrollment to reach the target sample size include graphic advertisements, periodical meetings with staff and repeated mailing actions.

All patients included in the trial, whether allocated to the study or control group, are managed in the same way according to protocols of pharmacological cardioversion. Such protocols are not specified by the trial, but they include standard components, comprising clinical evaluation, plasma electrolyte level assessment, baseline 12-lead ECG performance, continuous ECG monitoring, periodic noninvasive blood pressure (BP) control and an intravenous line.

Rate control medications, such as β-blockers or calcium channel blockers (diltiazem, verapamil), are allowed in the previous 2 h before study intervention. Chronic antiarrhythmic therapy is not an exclusion criterion—an AF episode indicates its low efficacy.

The assumptions of the study are explained to the patient and informed written consent is obtained. A case report form (CRF) is created for each patient. Investigators collect data regarding medical history, demographics, clinical presentation, previous and current treatment, and diagnostic test results. Both substances are prepared earlier in syringes by the study nurse unblinded to patient assignment. The study drug or placebo is administered intravenously in boluses by a nurse under the supervision of the enrolling physician, both blinded to patient assignment. In the case of serious adverse event occurrence, unblinding by the principal investigator is permissible, who will start the procedure for revealing a participant’s allocated intervention during the trial***.***

Each patient is observed within 2 h after the last bolus supply in order to determine efficacy and adverse reactions. The maximum concentration of canrenone is achieved within the first hour and decreases in two phases, with a mean half-life of 5–14 h, respectively [10].

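### Time to sinus rhythm restoration is assigned to ordinary continuous-variable methods, with no rule for the roughly 58 of 80 patients expected to have no conversion time at 2 h

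*Protocol article*

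**What the plan says.** The Endpoints section of the protocol article lists time to sinus rhythm restoration among the secondary endpoints. The Statistical analysis section names it as a quantitative variable, in one list with systolic and diastolic pressure and heart rate: "time to sinus rhythm restoration, SBP, DBP, HR), measures of location and dispersion will be calculated". The summary is mean and standard deviation, or median and quartiles if Shapiro-Wilk rejects normality. The test follows in a sentence that begins "For comparison of continuous variables between the two groups": unpaired t, or Mann-Whitney if the data are skewed. The section names no survival method and gives no value or rank to a patient who does not convert.

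The Study procedures section fixes the horizon: "Each patient is observed within 2 h after the last bolus supply in order to determine efficacy and adverse reactions". After that, "Further treatment of the patient will depend on their clinical condition and will follow appropriate clinical guidelines". The Sample size estimation section supplies the expected conversion: "We assume that the population fractions in the groups are 0.50 and 0.05". It also says that secondary endpoints are exploratory.

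**The concern.** Blood pressure and heart rate can be measured in every patient. A conversion time exists only for patients who convert. The rest are right-censored at 2 h, and any later conversion comes under open clinical management, so it no longer reflects the randomised bolus alone.

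If the listed methods are applied to the times that exist, each arm contributes only a subset chosen by the primary outcome. The groups compared are then no longer those formed by randomisation. A drug that converts many more patients could show no difference in time, or a longer mean, because late conversions enter mainly one arm. The Study objectives section gives conversion within a short time as the rationale for the trial, and this is the endpoint that addresses speed. The risk is a published statement of no difference in time to conversion when the drug works as assumed.

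**Working it through.** **Inputs.** Conversion by 2 h of 0.50 and 0.05, two-sided α 0.01 and power 90% (Sample size estimation); 80 patients allocated 1:1, so 40 per arm; horizon 2 h (Study procedures); analysis level 0.05 (Statistical analysis).

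**1. The plan's own figure.** Pooled-variance Z test, with mean proportion 0.275:

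n = [2.576·√(2·0.275·0.725) + 1.282·√(0.5·0.5 + 0.05·0.95)]² / 0.45² = (1.627 + 0.699)² / 0.2025 ≈ 26.7, so 27 per group. Power at 27 is 90.40%. Both match the protocol, so the rates below are the ones it used.

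**2. Patients without a time.**
- Canrenone: 40 × 0.50 = 20 convert and 20 do not.
- Placebo: 40 × 0.05 = 2 convert and 38 do not.
- Together: 58/80 = 72.5% have no time (50% of canrenone, 95% of placebo). At 27 per arm the share is the same.

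**3. What converters-only data would support.** Placebo converters follow Binomial(40, 0.05). No assumption about the shape of the times is needed.
- None: 0.95⁴⁰ = 0.129. No comparison is possible.
- At most one: 0.129 + 40·0.05·0.95³⁹ = 0.129 + 0.271 = 0.399 (from unrounded terms). There is no placebo standard deviation. With 20 versus 1, the smallest exact two-sided Mann-Whitney p is 2/21 = 0.095, so 0.05 cannot be reached.
- At most two: 0.677. Shapiro-Wilk, which chooses the summary, needs at least three values.
- At 27 per arm the first two become 0.250 and 0.606.

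**4. Effect on the answer.** This step assumes exponential conversion times, which the documents do not state. Rates per hour are λ = −ln(0.50)/2 = 0.3466 and −ln(0.95)/2 = 0.02565.
- Mean time among converters, 1/λ − 2e^(−2λ)/(1 − e^(−2λ)): 0.89 h versus 0.99 h. The tenfold difference in conversion nearly disappears.
- Restricted mean time to conversion over 2 h, (1 − e^(−2λ))/λ: 1.44 h versus 1.95 h, a difference of 0.51 h.

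**5. Simulation** (same model, 40 per arm, 2,000 trials per scenario, level 0.05):

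| Analysis | 50% vs 5% | Equal, 50% | Equal, 5% |
|---|---|---|---|
| Mann-Whitney, converters only | 3.1% | 4.9% | under 0.1% |
| Mann-Whitney, all patients, non-converters at 2 h | 99.9% | 4.4% | 3.6% |
| Log-rank, all patients | 99.9% | 4.5% | 3.6% |

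A further 4,000 trials of the Welch t test on times capped at 2 h gave 99.4% rejection at 50% versus 5%. Under equal rates it rejected in about 5% (rates of 50% or 20%) and 1.6% (rate of 5%).

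**The case against.** The strongest reply is that the article nowhere says non-converters are dropped. All patients share one fixed horizon. If non-converters are entered at 2 h, Mann-Whitney is a valid rank test, and with complete follow-up the mean of capped times is the 2-h restricted mean. The simulation bears this out: the listed tests then keep every patient, match the log-rank test and show no type I inflation. The Sample size estimation section also mentions intention-to-treat, which sits badly with discarding most of the sample. This much stands: one added sentence could rescue the Mann-Whitney test. But the sentence is not there, and the named methods do not supply it. Patients lost before 2 h, for whom the protocol allows 20% dropout, would still need a rule.

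Two further points stand. The log-rank result largely repeats the assumed difference in conversion, which the primary endpoint already tests, so the 3% versus 99.9% contrast should not be read as new evidence about speed. And a hazard ratio would be fragile too: with no placebo converter it has no finite estimate, and with about two it is very imprecise.

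It might also be said that the method belongs in a fuller protocol or analysis plan. That would answer a silence. Here the article names this variable and assigns it a method.

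**Conclusion.** The concern holds in a limited form. The plan gives a censored endpoint an unsuitable default and does not say how non-converters enter. On the plain reading, about 20 patients face 2, and the comparison cannot show the drug's effect on speed of conversion. The counts and binomial probabilities rest only on the protocol's 50% and 5% and 40 per arm. The simulated rates and mean times also rest on the exponential assumption.

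A reader might infer more, and the documents do not support it:
- That the plan prescribes a converters-only analysis. This is the natural reading, because a non-converter has no time, but it is an inference.
- That the test is invalid in the sense of too many false positives. The equal-rates runs show none; the fault is selection on a post-randomisation outcome and loss of information.
- That the trial's main conclusion is at risk. The primary endpoint is binary conversion by 2 h, with its own test. The sample size does not depend on this variable, and secondary endpoints are declared exploratory.

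Severity is therefore moderate: it should be fixed, but it does not stand in the way of the trial.

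**What to change.** Take "time to sinus rhythm restoration" out of the list shared with blood pressure and heart rate, and state its analysis separately:

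- Include all randomised patients, with Kaplan-Meier curves by arm, censored at 2 h or at loss to observation if earlier.
- Compare arms by log-rank test, labelled exploratory.
- Report the 2-h restricted mean difference with its interval as the estimate. With no placebo converter and full follow-up the placebo restricted mean is simply 2 h, so the difference can still be computed, although that arm's estimated variance is then zero. Do not rely on a hazard ratio.

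An acceptable alternative is to keep Mann-Whitney and state in advance that all non-converters share the rank at 2 h. This suits patients with complete 2-h follow-up and needs a separate rule for those lost earlier. Times among converters may be described within each arm, but not tested between arms.

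The cost is wording only. Study procedures already provides continuous ECG monitoring and an ECG when sinus rhythm returns, so no new data are needed. The change should be made before anyone sees unblinded results, including the planned look after 20 patients; if that look has already taken place, the date of the change should be recorded.

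### Two tests named for continuous variables cannot do their job in the branches where they apply: the rank sum test for skewed matched data, and Cochran's C for two means with unequal variances

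*Protocol article*

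**What the plan says.** The Statistical analysis section of the protocol article lists the quantitative variables as "time to sinus rhythm restoration, SBP, DBP, HR". It then sets out these branches.

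- **Description.** Mean and SD for normally distributed variables, otherwise "median and quartile range for variables for which the Shapiro–Wilk test null hypothesis has been rejected".
- **Between arms.** The sentence opens "For comparison of continuous variables between the two groups, the unpaired Student’s" t test. In brackets it offers Cochran's C as the alternative "test in the case of heteroscedasticity of variance) will be used, or for skewed data, the nonparametric Mann–Whitney" U test.
- **Within arms.** "Differences for matched samples (within groups) will be evaluated with McNemar’s test", the paired t test, or the test in "test or Wilcoxon’s rank sum test".

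The categorical variables, including sinus rhythm restoration and the safety outcomes, go to a χ² test with continuity correction or to Fisher's exact test. The Sample size estimation section declares the secondary and safety endpoints exploratory.

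**The concern.** The rank sum test treats its two samples as independent. Applied to before-and-after values from the same patients, it discards the pairing and uses a variance that is too large when the two values are positively correlated. It is also the Mann–Whitney U test under another name. The section therefore gives one procedure to both independent and matched data, and names no paired rank test.

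Cochran's C asks whether the larger of a set of variances is out of line with the others. It contains no means. Yet the section puts it forward as the replacement for the t test when variances differ, which is when a valid comparison of means is still needed.

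At stake are the within-arm changes in SBP, DBP and HR when they are skewed, and the between-arm comparisons of SBP, DBP, HR and time to sinus rhythm restoration when the variances differ. Time to sinus rhythm restoration is a listed secondary endpoint. It has no before-and-after pair, so only the Cochran's C problem reaches it.

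**Working it through.** **1. The plan's own figure, to see whether it is touched.** Inputs from Sample size estimation: 0.50 and 0.05, two-sided α 0.01, power 90%. With the pooled Z test, p̄ = 0.275:

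n = [2.576·√(2 × 0.275 × 0.725) + 1.282·√(0.25 + 0.0475)]² / 0.45² = (1.627 + 0.699)² / 0.2025 ≈ 26.7, so 27 per group.

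Power at 27 is 90.40%. The stated figures reproduce, and neither misnamed test enters them.

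**2. Which branches fail.**

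| Situation | Test named | Suitable? |
|---|---|---|
| Between arms, normal, equal variances | unpaired t | yes |
| Between arms, unequal variances | Cochran's C | no |
| Between arms, skewed | Mann–Whitney U | yes |
| Within arm, binary | McNemar | yes |
| Within arm, normal | paired t | yes |
| Within arm, skewed | rank sum | no |

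The section does not say what selects among the within-arm tests. That skewness selects the rank test is inferred from the between-arm rule.

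**3. Rank sum test on pairs.** For within-patient correlation r, the difference between two means has variance proportional to 2(1 − r), while an independent-samples test assumes 2. The nominal cut-off of 1.96 then acts like 1.96/√(1 − r). At r = 0.5 this is 1.96/0.707 = 2.77, so the true error rate falls well below 5%.

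Simulated with 40 pairs (80 patients, 1:1), lognormal values and two-sided 0.05:

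| r | Rank sum, no shift | Signed rank, no shift | Rank sum, 0.4 SD log shift | Signed rank, 0.4 SD log shift |
|---|---|---|---|---|
| 0.5 | 0.9% | about 5% | 37% | 60% |
| 0.7 | 0.1% | about 5% | 35% | 82% |

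The signed-rank power depends on how skewed the data are. A log-scale SD of about 1 reproduces the 60% and 82% to within a point (20,000 runs). A milder log-scale SD of 0.4 gives about 66% and 86%, with the rank sum test still at 37% and 35%. For a 0.5 SD log shift with log-scale SD 0.4, power is 60% against 84% at r = 0.5 and 63% against 97% at r = 0.7. With 32 pairs (20% dropout: 40 × 0.8) it is 48% against 74% and 47% against 91%. At r = 0 the rank sum test loses nothing.

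**4. Cochran's C between two arms of 40.** For two groups, C = max(s₁², s₂²)/(s₁² + s₂²). No mean appears. The two-sided 5% critical value is F/(1 + F) with F = 1.89 on 39 and 39 degrees of freedom, which is 1.89/2.89 = 0.654. With an SD ratio of 2 the expected value is near 4/(4 + 1) = 0.80, above that limit whatever the means are.

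| Mean difference | SD ratio | Cochran's C rejects | Welch rejects |
|---|---|---|---|
| 0 | 2 | 99% | 5% |
| 1 SD of the smaller-variance arm | 2 | 99% | 79% |
| 1 SD | 1 | 5% | 99% |

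The first two rows lie in the branch where the plan would use the test: the answer is the same whether or not the means differ. The last row lies outside that branch and only shows that the statistic is blind to means.

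**The case against.** The strongest reply is that both are naming slips. The text says that the samples are matched and that the variances are unequal, it sets the rank sum test beside McNemar's and the paired t test, and it names Mann–Whitney separately for the arms. Signed-rank and Cochran–Cox were probably meant, and an experienced statistician would probably run those. This is plausible and is a reason to rate the point low. It does not remove the point, because the text as it stands names specific procedures and nothing in it points to the intended ones.

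A reader might infer several stronger things that the document does not support.

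- **That all blood pressure and heart rate comparisons would be wrong or missing.** Four of the six situations in the table above have a suitable test.
- **That the rank sum test would produce false positives.** With positive correlation it does the reverse.
- **That the safety reading is compromised.** The listed blood pressure safety outcome is hypotension below 90 mmHg, a categorical outcome tested by χ² or Fisher's exact test. Continuous SBP, DBP and HR are not listed endpoints.
- **That power figures from normally distributed pairs describe the loss.** Such pairs would go to the paired t test, so the figures above use skewed data.
- **That the between-arm comparison is invalid because it ignores baseline.** The section does not say whether post-dose values or changes are compared, nor that within-arm tests will serve as treatment comparisons. An unadjusted randomized comparison is valid, and covariate adjustment is commonly left to an analysis plan.

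**Conclusion.** The point holds for two conditional branches and is minor. Both named tests are wrong for their stated task, and this can be seen from the one paragraph without any assumption. Followed literally, the within-arm slip costs roughly 23 percentage points of power at correlation 0.5 (60 − 37) and 47 at 0.7 (82 − 35). The between-arm slip replaces a test of means by a test of spread. The sizes rest on an assumed lognormal shape, shift, within-patient correlation and SD ratio, none of which the document gives. The directions do not depend on the particular values, provided that the paired values are positively correlated and the variances do differ. No conclusion about the primary endpoint depends on either branch.

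**What to change.** In the Statistical analysis section, name the Wilcoxon signed-rank test for matched samples in place of the rank sum test, and the Welch (or Cochran–Cox) t test in place of Cochran's C. State also that skewness is what selects the signed-rank test over the paired t test, if that is the intent. This costs a change of wording before analysis, with no new data and no change in sample size.

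Optionally, compare post-dose SBP, DBP and HR between arms by ANCOVA on arm and baseline value, and treat within-arm change as descriptive. Relative to an unadjusted comparison of post-dose values, the variance is multiplied by about 1 − r²: 0.75 at r = 0.5 and 0.51 at r = 0.7, with r assumed. This is a gain in precision and not the correction of an error. It adds a model to be specified, so it costs slightly more than the two name changes.
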